##### Comparison participants

Inclusion criteria for comparison participants are: (1) being 18 years or older; and (2) currently living in the comparison neighborhood as their primary or permanent residence at the time of recruitment.

#### Sample size

A total of 175 agrihood participants and 175 comparison participants will be recruited (*N* = 350). See Figure 1 for the flow and organization of participants.

**Figure 1 fig1:**
[figure not shown]
Flow and organization of participants.

##### Sample size estimation

Power was computed for a natural experiment evaluation (NEE) using Difference-in-Difference (DiD) analysis. For Aim 1, we calculated sample size for a Type I error rate alpha of 0.05, power of 0.8 for comparing the means between two groups considering physical activity outcomes of moderate-to-vigorous physical activity (MVPA); light, moderate, and vigorous physical activity (LMVPA); and time spent in sedentary behavior. Prior research has shown observed effects of moving to an activity-friendly community ranging between 10.4–10.9 min/day of MVPA, indicating small effect sizes of 0.40–0.42 (Cohen’s D) (7). We conservatively powered this study to detect a smaller effect size (Cohen’s D = 0.35). We estimate a sample size of 129 per group will provide adequate power to detect an effect size of Cohen’s D = 0.35 for all physical activity outcomes. The effect size of 0.35 is a conservative estimate based on current literature, equating to minimal detectable differences between 7.9 and 9.6 min/day for MVPA using estimates of standard deviation from previous studies (7, 33–37). This sample size is also adequate for a minimal detectable difference of 13.3 min/day for LMVPA. This sample size is adequate to detect effect sizes that are small to medium for all outcomes based on calculations for other aims. Prior community sampling of an NEE examining accelerometer-measured MVPA found a 20.64% attrition rate from baseline to year 1 and a 6.63% attrition rate from year 1 to year 2 (33). Given recently reported challenges to NEE recruitment, we conservatively overestimate attrition rates, necessitating a sample size of 175 for the agrihood and comparison groups.

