To conduct Aim 1, we will recruit two longitudinal cohorts, one of new agrihood residents (*N* = 175), and one of current comparison neighborhood residents (*N* = 175). Agrihood participants completing the baseline assessment will receive $100, those wearing an accelerometer and completing a mid-point survey will receive $150, and those completing the 6-month follow-up will receive $100. Comparison participants will only complete surveys and will receive $50 for the completion of a survey at each timepoint. Physical assessments will be conducted among agrihood participants by trained clinical staff in Mobile Health Assessment Centers (MHACs), which are mobile clinic spaces specifically designed for biometric data collection. MHAC measures will include blood pressure, resting heart rate, hemoglobin A1c (HbA1c), lipids, dermal carotenoids, weight and height. Seven-day accelerometer data collection will occur at baseline, mid-point, and 6-month follow-up to measure 24-h movement behavior (physical activity, sedentary time, and sleep). Geospatial data regarding access to food and physical activity resources, and resource utilization, will be collected as part of each survey timepoint. Locations of food and physical activity resources located within a 5-mile radius of the agrihood and comparison neighborhoods will be obtained via Google Distances API and mapped using ArcGIS. This will help us understand the food and physical activity resource context that these communities are located in. However, just because a resource is located proximally to a neighborhood, does not mean it is utilized (28). Therefore, we also will be asking questions to participants regarding their food acquisition and physical activity behaviors to understand how participants engage in the food and physical activity built environment. These questions include addresses of resources used, frequency of use, and time spent at resources. Survey measures for both agrihood and comparison participants include the Mediterranean Eating Pattern for Americans Screener (MEPA-16) dietary assessment (29), American Heart Association (AHA) Life’s Essential 8 (30), Perceived Stress Scale (31), and Brief Sense of Community Scale (32). The total time commitment for participants at each time point will last approximately 90 min, not including accelerometer wear time. In addition, a subsample of agrihood residents (*n* = 20) will be asked to provide an online 24-h dietary recall. See Table 1 for a detailed description of each outcome measure.

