
We will use the same strategy above to compare changes in food sourcing and dietary intake between groups across 3 time points (Agrihood: 0, 3 months after move-in date, 6 months after move-in date; Comparison: 0, 3, 6 months) using DiD analysis. MEPA-16 score will serve as the main dietary intake outcome for all participants, while ASA-24 nutrient and food group data will be examined among the Agrihood subsample. We will also compare the changes in number of food resources (by type), distance (in miles) to closest objectively measured food resources, and distance (in miles) to utilized food resources and associated changes in time spent in transportation to food resources between the groups across three time points (Agrihood: 0, 3 months after move-in date, 6 months after move-in date; Comparison: 0, 3, 6 months) using DiD analysis. We will assess if any of these variables are associated with dietary intake using linear mixed-effects multilevel models, with MEPA-16 score as the main outcome of interest. We will generate maps showing changing patterns in food resource utilization in ArcMap. Similar to the physical activity built environment, this approach of mapping and analyzing objective food resource environments, food resource utilization, and time use behaviors can help better understand how the built environment in these communities are or are not conducive to improving food access, connection to agriculture, and healthy eating, as well as how participants are (or are not) engaging in the resources designed to promote connection to agriculture and healthy eating.

In addition, we will explore the impact of social connection and loneliness on physical activity and healthy eating using the same DiD analyses but including social connection and loneliness terms into each of the regression models. We will analyze the survey data for loneliness and social connection over time using random effects models to assess change, and determine factors related to the changes. Additionally, we will explore mediation models using the changes in loneliness/connection scores as mediators for physical activity and dietary intake changes, using methods for analysis of mediation in generalized linear models.

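### The claim of adequate power for all outcomes is too broad: it cannot cover the ASA24 dietary recall, taken in 20 agrihood residents with no comparison group

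*Protocol article*

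**What the plan says.** The Sample size estimation section of the protocol article sets a "Type I error rate alpha of 0.05, power of 0.8 for comparing the means between two groups", applied to physical activity outcomes. It chooses the effect size as follows: "We conservatively powered this study to detect a smaller effect size (Cohen’s D = 0.35". The result is: "We estimate a sample size of 129 per group will provide adequate power to detect an effect size of Cohen’s D = 0.35", and this is raised to 175 per group for attrition. The section then extends the conclusion beyond physical activity: "This sample size is adequate to detect effect sizes that are small to medium for all outcomes based on calculations for other aims".

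Three other places bear on the dietary recall:

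- Study aims and approaches: "a subsample of agrihood residents (*n* = 20) will be asked to provide an online 24-h dietary recall". The same section says that comparison participants complete surveys only.
- Table 1, the list of Aim 1 outcome measures, has a row for the dietary recall and marks it as a subsample measure using ASA24.
- Data analysis makes the MEPA-16 score the main dietary outcome in all participants, and adds that "ASA-24 nutrient and food group data will be examined among the Agrihood subsample". It names no test, effect size or power for ASA24.

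**The concern.** The statement about all outcomes rests on a comparison of two groups of 129. The ASA24 recall has one group of at most 20 people, which is less than one sixth of one evaluable group (20/129 = 0.155), and nobody to compare them with. The only change analysis available is within person, over the three planned recalls. Adequacy for small-to-medium effects therefore cannot carry over from the main calculation.

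What is at stake is interpretation. ASA24 is the only recall-based dietary measure and the only source of nutrient data. If the power sentence stands unqualified, a non-significant ASA24 change could be taken as an adequately powered null on diet, and possibly set against a MEPA-16 result. The article does not say it would be read that way, but nothing in the sentence prevents it.

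**Working it through.** **1. The plan's own figures.** Inputs from Sample size estimation: d = 0.35, alpha 0.05, power 0.80. Sidedness is not stated; two-sided reproduces the figure, whereas one-sided would give 101.

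- n per group = 2(1.960 + 0.842)²/0.35² = 128.1, rounded up to 129. The t-based solution is 129.1, and power at 129 per group is 0.80.
- Attrition, from "20.64% attrition rate from baseline to year 1 and a 6.63% attrition rate from year 1 to year 2": retained fraction = (1 − 0.2064)(1 − 0.0663) = 0.741. Then 129/0.741 = 174.1, so 175, matching "A total of 175 agrihood participants and 175 comparison participants will be recruited".

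Both figures reproduce.

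**2. ASA24 subsample, effect in SDs of the within-person change.** Input: n = 20, agrihood only. Method: two-sided paired (one-sample) t-test, alpha 0.05, noncentrality = d_z × √n, with n − 1 degrees of freedom. The n = 15 column is an assumption: it applies the plan's ratio 129/175 = 0.74 to 20 people (14.7, about 15). The article states no attrition for the subsample.

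| Change (SD of change) | Power, n = 20 | Power, n = 15 (assumed) |
|---|---|---|
| 0.20 | 0.14 | 0.11 |
| 0.35 | 0.32 | 0.24 |
| 0.50 | 0.56 | 0.44 |
| Detectable at 80% power | 0.66 | 0.78 |

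About 66 to 67 completers would be needed for 80% power at 0.35 SD of change.

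**3. ASA24 subsample, effect of 0.35 on the outcome SD.** The conversion needs a within-person correlation rho, which the article does not give, so a range is assumed.

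- Baseline against one follow-up: d_z = 0.35/√[2(1 − rho)].
- Baseline against the mean of the 3- and 6-month recalls, assuming equal variances and equal correlations: d_z = 0.35/√[1.5(1 − rho)].

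| rho | Power, one follow-up, n = 20 | Power, mean of two follow-ups, n = 20 |
|---|---|---|
| 0.2 | 0.22 | 0.27 |
| 0.5 | 0.32 | 0.40 |
| 0.7 | 0.48 | 0.60 |
| 0.8 | 0.65 | 0.77 |

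None of these reaches 0.80. With one follow-up, that would take rho of about 0.86.

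**4. A medium effect of 0.5 on the outcome SD, one follow-up, n = 20.** d_z = 0.5/√[2(1 − rho)] gives power 0.56 at rho 0.5, 0.78 at rho 0.7 and 0.92 at rho 0.8. At the upper end of the small-to-medium range, adequacy therefore turns on the unknown correlation.

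**The case against.** The best case for leaving the sentence alone has five parts.

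- **No figure is wrong.** The 129 and 175 are correct, and the article attaches no power figure to ASA24. This stands: the fault is in the scope of one sentence.
- **The subject of the sentence is the full sample size.** It can be read as covering only outcomes measured at that size, since the recall is openly labelled a subsample. This is a charitable reading, but the words make no such restriction and Table 1 counts the recall among the outcome measures.
- **The calculations for other aims are not shown and may cover it.** Dietary intake belongs to Aim 1, and no unseen calculation makes 20 people in one group adequate for small effects on ordinary assumptions: at 0.2 SD of change, power is 0.14.
- **ASA24 is supplementary.** MEPA-16 is the main dietary outcome and the Discussion calls the study a pilot. This stands, and it keeps the point minor.
- **The same sentence reaches further elsewhere.** The Discussion's limitations say accelerometer and biological measures are also taken only in the agrihood. That is true; limiting the sentence to outcomes measured in both cohorts would exclude those too.

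A reader might infer something stronger: that power for ASA24 is 0.2 to 0.4 where the plan promised 0.80 at d = 0.35, or that small-to-medium effects are simply undetectable. The document supports neither. It ties 0.35 and 0.80 to physical activity outcomes and to a between-group difference; for the rest it says only small to medium. The 0.2 to 0.4 range holds for low to moderate correlations, and a medium effect on the outcome SD can exceed 80% power if the correlation is high. The 15-completer case also borrows attrition observed over two years for a six-month follow-up.

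**Conclusion.** The sentence is wrong as written for the ASA24 recall. With 20 people in one group, a two-sided paired t-test at alpha 0.05 has 80% power only from about 0.66 SD of change, or 0.78 SD if 15 remain. For an effect of 0.35 on the outcome SD, power is about 0.22 to 0.65 over correlations of 0.2 to 0.8, or 0.27 to 0.77 if both follow-ups are averaged against baseline. These ranges rest on assumed correlations, the 15 on an assumed retention, and the averaged figures on equal variances and correlations across recalls. No allowance is made for examining several nutrients. The main sample size is unaffected. This is a minor correction to an over-broad power claim.

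**What to change.** - **Sample size estimation:** limit the adequacy sentence to outcomes measured in both full cohorts; for diet, that is MEPA-16. Add that the ASA24 subsample (n = 20, agrihood only) has 80% power only for within-group changes of about 0.66 SD of change, and that this rises if people are lost (0.78 SD with 15).
- **Data analysis:** say that ASA24 results will be reported descriptively, as within-group mean changes with 95% confidence intervals, and that a non-significant change will not be read as evidence of no dietary change. The role of MEPA-16 stays as it is.

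The cost is a few sentences. No participants, measurements or redesign are needed; the stated power claim becomes less favourable.

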##### Loss to follow-up

A participant will be considered lost to follow-up if they fail to return for any of the scheduled follow-up visits, or do not complete that timepoint’s survey, and cannot be contacted by the research team by the end of the study period. In the case of loss to follow-up or withdrawal, partial data will be used in the data analysis with multiple imputation used to address missing data where appropriate. Intent-to-treat will be used to preserve the group allocation in our analysis (38).

### Data collection

The research team conducted an initial survey of demographic and health indicators, neighborhood design preferences, and willingness to pay for specific amenities among 128 prospective buyers of the agrihood between March and July 2024 (Baylor IRB #2158321–1). Findings from the survey provided a formative understanding, which helped to inform the design of the present study and served as a project pilot test for survey recruitment and enrollment procedures (39, 40).

Beginning in Spring 2025, data collection began across three time points (pre-move-in, 3 months after move-in date, and 6 months after move-in date) by trained research and clinical staff (see Table 1). Over the course of 6 months, agrihood participants will be asked to complete (1) three 30-min online surveys; (2) two 30-min in-person health assessments collecting height, weight, blood pressure reading, heart rate, dermal carotenoid scan (Veggie Meter®), HbA1c (finger prick), and lipids (finger prick); (3) three 7-day consecutive accelerometer wears; and (4) three 30-min online dietary recalls (subsample). Comparison participants will be asked to complete three 30-min online surveys at 0 months, 3 months, and 6 months from recruitment.

The focus groups are planned to occur starting in the Fall of 2025. The accompanying one-week time-use study, entailing once-daily self-reports, will begin the following day after each of the four focus group sessions. The gathering of economic data will occur during focus group discussions and concurrently with the agrihood developer as homes continue to be built and residents move into the new units. The developer survey will be designed to capture the full economic arc of an agrihood project—from conception to financial stabilization—by prompting developers to narrate each phase of development (e.g., project origins and strategic intent, land acquisition and zoning, entitlement and permitting processes, capital investment structures, farm-related costs and revenue projections, marketing, sales absorption rates, and plans for long-term stewardship).

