## Materials and methods

### Design and setting

The *Neighborhood & Health Study* employs a quasi-experimental prospective case–control mixed-methods approach. This entails assessing new residents of the agrihood and a comparison group over a period of 6 months (subject to a + 3-month adjustment based on actual move-in date).

The study is primarily situated at Indigo, a new 235-acre, planned 750-home agrihood located in Richmond, Texas (Fort Bend County), about 28 miles southwest of downtown Houston (18). Its developer, Meristem Communities Development Firm, is a Houston-based real estate development firm committed to creating Places for People™ which they envision as being inclusive public spaces (19). Meristem emphasizes resiliency and human-centric design by mindfully and sustainably creating places that connect land, natural systems, and people. For this reason, among others (e.g., proximity to the research team, a development timeline that aligns with the research project timeline, and Meristem’s willingness to partner), Indigo was selected for this study.

The agrihood comprises 42 acres of farm and pasture, over half of the community dedicated to open space, a 12-acre mixed-use town center with a walkable main street design and mixed retail/businesses, a 25-acre lake, integrated trails, “the Filling Station” (welcome center, café, gathering place, farm stand), vehicle-free community areas focused on nature, and spaces for residents to interact and play between rows of houses where there would traditionally be a street. Agriculture in the agrihood will be managed by Agmenity (20), a leader in the local and national agrihood movement, and will include crop fields, orchards, pasture for livestock, year-round production of seasonal produce, farm stand, farm club, agricultural education opportunities, programming, volunteer opportunities, and pastured poultry and egg production. The agrihood was designed to provide a foundational connection to agriculture and a people-first approach that fosters community connection and overall health, while being committed to environmental stewardship.

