##### Agrihood participants

Inclusion criteria for agrihood participants are: (1) being 18 years or older; and (2) living in the agrihood as their primary or permanent residence for less than 3 months (cohort) or at least 4 months (focus group) at the time of recruitment.

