### Data analysis

For Aim 1, we will compare the changes in physical activity outcomes (moderate to vigorous physical activity [MVPA], light, moderate, and vigorous physical activity [LMVPA], walking, sedentary behavior) between the agrihood and comparison participant groups across three time points (Agrihood: pre-move-in, 3 months after move-in date, 6 months after move-in date; Comparison: 0, 3, 6 months) using DiD analysis (linear mixed-effects longitudinal models). Regression models will include the group, time period, and the group by time period interaction terms. Random cluster effects will be included to account for correlations between participants in the same neighborhood and *a priori* covariates of age, sex, and educational attainment. Random effects for the participants will be included to account for correlation in observations. To address multicollinearity, we will assess variance inflation factors (VIF > 5) and pairwise correlations (|r| > 0.70); collinear variables will be excluded, combined, or tested in sensitivity analyses to avoid attenuation of the group × time effect. Confounders showing baseline imbalance (standardized mean difference > 0.10) will be prioritized for inclusion. Restricted maximum likelihood will be used for complete case analysis to incorporate all available data, and intention-to-treat analysis will include all participants included at baseline. Multiple imputation will be used to estimate missing data points and standard errors. Imputations will follow standardized procedures, including auxiliary variables, and will follow hierarchical approaches. We will examine the potential for missingness of data to not be at random by comparing baseline characteristics of participants who have completed physical activity data with those who do not. If there are differences by age, education, race, or self-reported perceived health, any variables that differ will be used as an auxiliary variable in multiple imputation. Fraction of missing information will be used to measure level of uncertainty about the values imputed for missing values. We will use a number of imputations that satisfy the recommendation to have the number of imputations (at least) equal the highest fraction of missing information (FMI) percentage. Using the geographic information system (GIS) data and resulting maps, for physical activity resources we will: (1) count the number of resources located within the 5-mile network buffer using ArcGIS; (2) measure the distances to the closest resources for different types of resources (e.g., closest park or trail) using ArcGIS and Google Distances API; (3) assess how these counts and distances change over time; and (4) assess changes in time spent in transportation to go to resources. Specifically, we will compare the changes in number of physical activity resources, distance (in miles) to closest objectively measured resources, and distance (in miles) to utilized resources and associated transportation-related time spent between the groups across 3 time points (Agrihood: 0, 3 months after move-in date, 6 months after move-in date; Comparison: 0, 3, 6 months) using DiD analysis, and assess if any of these variables are associated with device-measured physical activity outcomes using linear mixed-effects multilevel models. All statistical analysis will be conducted using SAS and/or R software. We will also generate maps showing changing patterns in physical activity resource utilization in ArcMap. This two-pronged approach of mapping and analyzing objective physical activity environments as well as physical activity resource utilization and time use behaviors are important to better understand how the built environment in these communities are or are not conducive to physical activity, as well as how participants are (or are not) engaging in the resources designed to promote physical activity.

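### Agrihood visits run on a move-in clock and comparison visits on a recruitment clock, yet both enter one difference-in-differences time factor with no calendar or season term

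*Protocol article*

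**What the plan says.** The Design and setting section describes both groups as followed "over a period of 6 months (subject to a + 3-month adjustment based on actual move-in date"). Only the agrihood group has a move-in date during the study. The Discussion states that comparison participants are existing residents.

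The Data collection section sets the agrihood visits before move-in and at 3 and 6 months after it. For the comparison group it says: "Comparison participants will be asked to complete three 30-min online surveys at 0 months, 3 months, and 6 months from recruitment".

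The Data analysis section puts the two schedules side by side as the three time points of one analysis: "Agrihood: pre-move-in, 3 months after move-in date, 6 months after move-in date; Comparison: 0, 3, 6 months". It then states: "Regression models will include the group, time period, and the group by time period interaction terms". The covariates fixed in advance are "covariates of age, sex, and educational attainment", and confounders that are unbalanced at baseline get priority for inclusion. Food sourcing and dietary intake follow the same strategy, with MEPA-16 as the main dietary outcome.

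The eligibility rule for the agrihood cohort reads differently from a pre-move-in baseline. At recruitment the person must be "living in the agrihood as their primary or permanent residence for less than 3 months (cohort").

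**The concern.** Difference-in-differences removes a time effect that both groups share, provided that both are observed over the same span or that the model accounts for the dates. Here the same time label can stand for different elapsed times and different months of the year in the two groups. Produce intake, gardening, outdoor activity and time in green space plausibly vary with season, and the survey measures all of them in both groups. With misaligned dates, part of the seasonal change does not cancel. It lands in the group-by-time term, which is the study's estimate of the agrihood effect. The limitations in the Discussion concede that the comparison group has no pre-move baseline, but they do not mention the two clocks.

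**Working it through.** **The plan's own figures.** The plan gives no figure on visit alignment to reproduce. The sample size (129 per group, 175 after attrition) is not affected by this point.

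**Elapsed time.** Let g be the months from agrihood baseline to move-in. The agrihood follow-ups then fall 3 + g and 6 + g months after baseline. The comparison surveys fall at 3 and 6 months.

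| g (months) | Agrihood, 3-month label | Agrihood, 6-month label | Comparison |
|---|---|---|---|
| 0 | 3 | 6 | 3 and 6 |
| 1.5 | 4.5 | 7.5 | 3 and 6 |
| 3 | 6 | 9 | 3 and 6 |

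The range 0 to 3 comes from the 3-month adjustment in Design and setting. At g = 3 the agrihood 3-month visit has the same elapsed time as the comparison 6-month survey. For any g above 0, the calendar dates cannot match at both baseline and follow-up.

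**How firm that range is.** It is not firm, because four places in the protocol do not fit together:
- Design and setting allows an adjustment of 3 months, tied to the actual move-in date.
- Data collection started in Spring 2025 with a pre-move-in assessment, while the setting description schedules the first move-ins for fall 2025. That allows gaps longer than 3 months.
- The eligibility rule admits people already resident for up to 3 months. For them g would be negative. At g = −3 the 6-month label falls only 3 months after baseline.
- The GIS and dietary analyses label the agrihood baseline as 0, while the physical activity analysis labels it as pre-move-in.

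**Seasonal contrast.** Assume a sinusoidal season with a 12-month period and amplitude a (half the peak-to-trough range), and the same baseline date in both groups. The baseline terms cancel, and the false contrast at the last visit is s(t+6+g) − s(t+6). Its maximum over start month t is 2a·sin(πg/12).
- Every g = 3: 2a·sin(π/4) = 1.41a.
- Every g = 1.5: 2a·sin(π/8) = 0.77a.
- g uniform over 0 to 3 months: the phase shift θ is uniform over 0 to π/2, and the mean of e^(iθ) is (2/π)(1 + i) = 0.637 + 0.637i. The maximum is a·|0.637 − 1 + 0.637i| = a·√(0.132 + 0.405) = 0.73a.

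**Illustration.** The protocol gives no seasonal amplitude, so the following values of a are assumptions, in outcome standard deviations.

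| Assumed a (SD) | Every g = 3 | g uniform over 0 to 3 |
|---|---|---|
| 0.05 | 0.07 | 0.04 |
| 0.10 | 0.14 | 0.07 |
| 0.20 | 0.28 | 0.15 |

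These are worst-month values. Spreading start months within a shared calendar lowers them. If the two groups are recruited in different months, the shared-baseline assumption fails and these figures are no longer bounds.

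**Do the stated terms remove it?** No. Age, sex and education do not carry the date of a visit. A baseline covariate entered as a main effect shifts the level of the outcome, not its change, so the baseline-imbalance rule does not help either.

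**The case against.** Timing agrihood follow-up from move-in is a defensible choice, because it fixes the length of exposure at 3 and 6 months. Nor does difference-in-differences strictly require matched calendar spans, since calendar effects can be modelled from visit dates. Both points stand, but the model as written does no such modelling.

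The article does not give recruitment months for the comparison group. Concurrent enrolment may be intended, and a full protocol or analysis plan may add a season term. That also stands, so nobody can say that the calendars are in fact unrelated. However, the article itself fixes the two clocks and the core model terms. A later analysis plan could add calendar month, but it could not create an overlap of seasons that scheduling had failed to produce.

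A reader might make three stronger inferences, none of which the documents support:
- **That agrihood follow-up is definitely 6 to 9 months.** The eligibility rule and the Spring and fall 2025 dates allow shorter and longer intervals.
- **That the seasonal error can be set against the 7.9 to 9.6 min/day detectable difference for MVPA.** The Discussion says that accelerometers are worn only in the agrihood, so no two-group device-measured contrast exists for this error to enter. That is a separate problem.
- **That the error favours the agrihood.** Its sign depends on enrolment dates that are not given.

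**Conclusion.** The concern holds for the two-group survey outcomes: MEPA-16, self-reported activity, produce intake and time in green space. As written, the plan lets seasonal differences enter the group-by-time term, and no stated term removes them. The direction is unknown. Under a sinusoidal season, a shared baseline date and gaps of 0 to 3 months, the worst case is 1.41 amplitudes if every gap is 3 months and about 0.73 if gaps are uniform. The amplitude itself is not in the documents, so the size on any outcome scale remains conditional. Separately, the statements on whether baseline precedes move-in, and by how long, contradict each other and must be reconciled. This should be corrected, but it does not by itself invalidate the study.

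**What to change.** 1. Add calendar month, or a seasonal harmonic, of the actual survey date to the two-group difference-in-differences models. This can also be done for data already collected, if survey dates are recorded. A single harmonic costs two parameters and month indicators up to eleven. Either works only where the groups overlap in calendar months.
2. Add a sensitivity analysis that uses actual months since baseline, or that is restricted to agrihood participants with a short gap between baseline and move-in. Elapsed time belongs here rather than in the main model: in the comparison group it is fully determined by time period (0, 3, 6), so only variation in the agrihood gap would identify it.
3. For comparison participants still to be enrolled or followed, schedule the online surveys in the same calendar months as agrihood baseline and follow-up visits. Full prospective matching is no longer available, because data collection has begun. Any extension of comparison follow-up must fit the 13-month funding window.
4. Reconcile Design and setting, Data collection and the agrihood inclusion criteria on when baseline occurs relative to move-in, and state the permitted gap.

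The cost is a few model parameters, rescheduled survey invitations and possibly longer comparison follow-up. No sample-size figure changes.
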